## Abstract

**Background:**

Research literature consistently documents that scientifically based therapeutic recommendations are not always followed in the hospital or in the primary care setting. Currently, there is evidence that some general practitioners in Australia are not prescribing appropriately for patients diagnosed with 1) hypertension (HT) and 2) chronic heart failure (CHF). The objectives of this study were to improve general practitioner’s drug treatment management of these patients through feedback on their own prescribing and small group discussions with peers and a trained group facilitator. The impact evaluation includes quantitative assessment of prescribing changes at 6, 9, 12 and 18 months after the intervention.

**Methods:**

A pragmatic multi site cluster RCT began recruiting practices in October 2009 to evaluate the effects of a multi-faceted quality improvement (QI) intervention on prescribing practice among Australian general practitioners (GP) in relation to patients with CHF and HT. General practices were recruited nationally through General Practice Networks across Australia. Participating practices were randomly allocated to one of three groups: two groups received the QI intervention (the prescribing indicator feedback reports and small group discussion) with each group undertaking the clinical topics (CHF and HT) in reverse order to the other. The third group was waitlisted to receive the intervention 6 months later and acted as a “control” for the other two groups.

De-identified data on practice, doctor and patient characteristics and their treatment for CHF and HT are extracted at six-monthly intervals before and after the intervention. Post-test comparisons will be conducted between the intervention and control arms using intention to treat analysis and models that account for clustering of practices in a Network and clustering of patients within practices and GPs.

**Discussion:**

This paper describes the study protocol for a project that will contribute to the development of acceptable and sustainable methods to promote QI activities within routine general practice, enhance prescribing practices and improve patient outcomes in the context of CHF and HT. Trial registration: Australian New Zealand Clinical Trials Registry (ANZCTR), Trial # 320870.

## Background

Pharmacological management of hypertension (HT) reduces cardiac events, stroke, hospitalisations, health care costs and improves quality of life for hypertensive patients (HT) [1,2]. Appropriate treatment of chronic heart failure (CHF) with ACE inhibitors, angiotensin II receptor antagonists, beta-blockers and diuretics have also shown benefits in terms of survival and averted hospitalisations, irrespective of the underlying cause [3,4].

Australian [5,6] and overseas studies report that treatment of HT [7-15] and heart failure [16-19] are not well aligned with evidence-based guidelines. For example, in Australia, fewer than 50 percent of heart failure patients admitted to any of three hospitals in Tasmania were being treated with target doses of the recommended drugs [18]. Among Australian patients attending general practice, under-prescribing for heart failure was found both in terms of the number receiving the recommended drugs and the dosage levels [20,21]. A national Australian survey reported the prevalence of untreated HT at 15.2% [13] and four consecutive GP audits of self-reported prescribing practices concluded that there was room for improvement in the management of hypertensive patients with co-morbidities [14].

The consequences of suboptimal care for these conditions include increased hospitalisation, higher mortality, [22,23] greater symptom severity [23] and increased costs to the health care system [22,24-26]. It is clear that best practice guidelines alone cannot secure improvements in practice [5,27-29].

Educational interventions and quality improvement (QI) activities can improve the quality of prescribing in general practice settings [5,30]. Multi-faceted interventions, particularly those involving interactive educational sessions for healthcare providers, and/or patient education are reported to be more effective than passive interventions [10,31-37]. Multi-faceted interventions have shown modest improvements in patient outcomes such as the proportion of patients meeting blood pressure targets [8,23] and also changes in prescribing patterns such as the proportion CHF patients receiving a beta blocker or taking target doses of ACE inhibitors [38].

In evaluating these types of complex QI interventions, pragmatic randomised controlled trials (RCTs) are emerging as a way of bridging the gap between traditional RCTs which have a good internal validity and observational studies, which have good external validity [39-41].

The Prescribing Data in General Practice Demonstration (PDGPD) project uses a multifaceted complex intervention aimed to improve GP prescribing behaviour for patients with HT and CHF in alignment with clinical practice guidelines.

This paper provides details of the intervention components and protocol, and methods and measurements used to evaluate the impact of the quality improvement initiative.

The project is a partnership between National Prescribing Service (also known as NPS MEDICINEWISE), an independent, evidence-based organisation delivering continuing education for health professionals to enable better decisions about medicines and medical tests [42], and the Australian General Practice Network (AGPN), the body representing a network of 111 local general practice networks (henceforth referred to as Networks) which covers 90% of registered GPs in the country [43].

The project governance included several external and internal groups that oversee various aspects of the project including the evaluation and the implementation. (see Additional file 1: Appendix 1).

## Methods/Design

### Aims of the intervention

The aim of the PDGPD intervention is to improve prescribing behaviour and clinical outcomes for patients with HT and CHF. These topics were chosen due to the existing gap between evidence and actual practice and the potential benefits resulting from changes in the management of patients. A list of terms used in clinical practice software to describe these two diagnoses can be found in Appendix 2 (Additional file 2). The quality improvement activity allows GPs to use their own prescribing data for ongoing review of patient management and for peer comparison.

### The intervention

The intervention included facilitated discussion about these conditions within general practices recruited across Australia using feedback about their patient management extracted from practice clinical software. This multi-faceted intervention was designed to be implemented from June 2009 with follow-up until December 2011.

We used a multifaceted intervention based upon recognised quality improvement strategies that are implemented over a 12 month time frame. The intervention in this project consisted of a series of quality improvement activities (Figure 1). Data cleaning and recording of relevant clinical information was actively encouraged two months prior to the first clinical meeting among all practices in the study (step 1) to enable extraction of reliable information from relevant database fields. An initial facilitated group discussion (*clinical meeting*) was held by GPs within the practice with a trained project facilitator on treatment of CHF and HT (step 2). A data extraction and report tool supplied immediate feedback from the practice clinical software system regarding each GP’s own prescribing, as well as the results for the whole practice and the local GP network for peer comparisons for each clinical meeting.

**Figure 1 F1:**
[figure not shown]
Quality improvement intervention process.

Identification of patients suitable for clinical review occurred after the initial clinical meeting (step 3). A follow-up facilitated peer group clinical meeting was held around two to three months after the first meeting (step 4) to check progress on the patients prioritised for review of therapy and any changes to the prescribing data feedback.

### Aim of the evaluation

The aim of the evaluation of the PDGPD project was to estimate the impact of the quality improvement intervention on prescribing practice and to measure short term changes in blood pressure in patients with HT and CHF. The evaluation used a pragmatic randomised cluster controlled trial design.

### Study groups and randomisation

Practices agreeing to participate were registered and randomly allocated automatically into one of the three study groups (either into one of the two intervention groups or into the wait-control group) using computer generated random numbers. Block randomisation was used to enable balanced representation of practices in each of the Networks. The randomisation determined the sequence of exposure to the intervention as follows (see Figure 2):

Group 1 received the intervention for the CHF topic in the first six months and the HT topic in the next six months. In the first six months, this group also acts as the topic control group for group 2.

Group 2 received the intervention for the HT topic in the first six months and the CHF in the next six months and also acts as topic control group for group 1 in the first six months.

Group 3 is a wait-control for groups 1 and 2 in the first six months and did not receive any intervention in the first six months. This group received the intervention after six months and implemented the 2 topics sequentially – the order of topics was left up to the practice involved to choose. This group acts as ‘true’ control for groups 1 and 2 in the first six months.

**Figure 2 F2:**
[figure not shown]
Evaluation using a cluster randomised controlled design. Group allocation and timeframes for data extraction and clinical meetings.

As it is well recognised with educational interventions delivered at the practice level [40,44], it was not feasible to blind participating general practitioners and practices to the intervention because they had to be trained on the software installation and needed to be notified of their topic allocation in order to carry out the required quality improvement activity.

The expected time frame for the research was 2 years, including the recruitment and training time and 18 months of follow-up; data collection for baseline and six months are currently being analysed.

### Outcome assessment

Diagnoses of HT and CHF were based on GP clinical decision entered in their database. Clinical indicators of appropriate and safe prescribing behaviour and blood pressure control were used as measures of impact at various stages of the intervention. This type of indicator is widely used in the medical literature, and Australian doctors are familiar with the concept from their exposure to locally relevant educational resources and interventions extracting data from their medical software for other quality improvement initiatives [45-47].

The impact of the intervention was measured by two primary prescribing outcomes for each condition targeted by the intervention and five secondary prescribing outcomes relating to these two clinical topics. These were largely based on the prescribing indicators used in the feedback reports to the GPs. For details of the medicines covered see (Additional file 3: Appendix 3). Hospital admission for heart failure was not used as a clinical outcome indicator in this study because the prescribing software database does not link to the data collection for hospital admitted patients and does not contain coded fields for this information.

### Primary prescribing indicators

#### Hypertension

Proportion of adult patients with a diagnosis of HT who have suboptimal control of blood pressure as follows:

a. Proportion of adult patients with HT and using at least one antihypertensive drug, whose latest blood pressure is 140 / 90 mm Hg or higher

b. Proportion of adult patients with HT and coronary heart disease, diabetes, chronic kidney disease, stroke or transient ischaemic attacks (TIA), whose latest blood pressure is 130 / 80 mm Hg or higher

#### Chronic heart failure

Proportion of adult patients with CHF receiving appropriate treatment, ie:

a. using an ACE inhibitor or angiotensin II-receptor antagonist

b. using an ACE inhibitor or angiotensin II-receptor antagonist and using a heart-failure-specific beta blocker

#### Chronic Heart Failure

1. Proportion of adult patients with CHF using an ACE inhibitor below the recommended dose

2. Proportion of adult patients with CHF using a drug that may exacerbate the disease (see Additional file 3:Appendix 3)

The clinical indicators used in this study were developed in consultation with clinical experts, GPs, pharmacists, consumers and policy makers via focus groups.

The decision on the final indicators to be measured was made on the basis of their construct validity, face validity and operability or availability for data extraction from routine collections. Most of the suggested indicators were adopted from a previously published NPS manual [45] or NPS audits. A comprehensive review of the evidence relating to each indicator was conducted to establish construct validity. Refinement to ensure face validity was undertaken during a large workshop with GPs and other potential users. Using a simple questionnaire with a Likert scale, participants were asked to rate the accuracy of the indicators for measuring good prescribing practice, the usefulness for identifying patients receiving suboptimal treatment, and the usefulness for comparing their own prescribing practice with that of other GPs.

Final indicator definitions were decided by consensus using the above evidence during clinical reference group meetings, with input from expert Australian GPs and other advisory or steering groups where necessary.

Final selection of 9 indicators from a set of 82 potential clinical indicators was followed by field testing. The indicators were included in the study if there was evidence of their potential to improve patient care in the general practice setting, and they could be automatically extracted from general practice clinical software. Blood pressure measurements used in this study were those taken during the course of routine clinical care. All blood pressure measurements available in coded fields were retrieved at each interval but the latest available blood pressure recorded for each patient within 12 months of the data extraction was generally used to determine the latest blood pressure level; and up to 12 blood pressure readings per patient in the past year were used to estimate the mean for the practice.

### Data collection for the impact evaluation

The extraction tool enables de-identification of GP and patient data, encryption and transfer of information to a secure NPS file transfer site for the evaluation.

Data extracts to estimate indicators for evaluation by group allocation was planned to occur every three months after the initial clinical meeting.

### Sample Size estimations

Sample sizes were calculated with an assumed intra-cluster correlation of 0.08 at the 80% power and 5% significance level using the University of Aberdeen sample size calculator, (version 1.0.2) which adjusts for the clustering of GPs and patients in practices [48]. Estimates for the ICC and other parameters were based on previous studies and analysis of data from a sample of general practices [49]. With more than one primary outcome to be measured, the sample size required for the trial had to be powered to detect changes for the condition with lower prevalence. In Australian general practice, we applied the CHF clinical indicators as the basis of the sample size calculations (estimated prevalence: 1%-4.1% for CHF vs. 10%-44% for HT) [50-52]. Data previously collected from an Australian GP panel source,[49] were used for the following calculations. Assuming each of the GPs saw at least half of their patient clientele in a year, it was estimated that around 3% of GPs patient population had CHF and that there are 7200 active adult patients in an average 3 GP practice, of which 86 patients with CHF were expected to visit the practice during the first 6 months of the study. For a three-arm study with ICC = 0.08, the total number of practices required to show this difference is 99. Further, based on previous Australian and overseas experiences of GP or practice recruitment in trials and surveys [19,53,54], with an estimated drop out rate of 40-50% of all clusters (practices), at least 180 practices were required to identify both sufficient cases of CHF (the smaller patient group) and observable changes such as 10% absolute increase in prescribing of ACE inhibitors and 15% absolute increase in prescribing of beta blockers.

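### The recruitment target of 180 practices keeps the required 99 only for drop-out up to 45%; at the stated upper limit of 50%, 90 remain

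*Protocol article*

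**What the plan says.** All the figures stand in one section of the Protocol article, Sample Size estimations.

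- Design values: an "assumed intra-cluster correlation of 0.08 at the 80% power and 5% significance level".
- Cluster size: "86 patients with CHF were expected to visit the practice during the first 6 months of the study".
- Requirement before attrition: "the total number of practices required to show this difference is 99", for three arms.
- Allowance for loss of practices, and the resulting target: "with an estimated drop out rate of 40-50% of all clusters (practices), at least 180 practices were required".
- Target differences: "10% absolute increase in prescribing of ACE inhibitors and 15% absolute increase in prescribing of beta blockers".

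The section Study groups and randomisation says that practices are "randomly allocated automatically into one of the three study groups". It gives no allocation ratio. The article does not say which drop-out rate within 40-50% produced 180, and no other section gives a numerical reserve of practices.

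**The concern.** The sentence sets a range of expected drop-out beside a minimum number of practices. A reader will naturally take the minimum as sufficient for the whole range, but it is sufficient only for the lower half. If half the practices leave, which the plan itself regards as possible, fewer practices remain than it says are required.

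What is at stake is how the result is read. With 50% attrition, an inconclusive ACE-inhibitor comparison would come from a trial with somewhat less than the 80% power quoted, and the article would not show this.

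**Working it through.** **Inputs from the document:** 99 practices required; drop-out 40-50%; target 180; ICC 0.08; 86 CHF patients per practice; 80% power; 5% significance; differences of 10 and 15 percentage points.

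**Assumptions where the document is silent:** two-sided test, equal allocation (33 practices per arm for 99), pairwise comparison of arms, and the baseline proportions named below.

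**1. Reproduce the target.** Practices to recruit = required / (1 − drop-out).

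| Drop-out | Practices to recruit | Left of 180 |
|---|---|---|
| 40% | 99 / 0.60 = 165 | 180 × 0.60 = 108 |
| 45% | 99 / 0.55 = 180 | 180 × 0.55 = 99 |
| 50% | 99 / 0.50 = 198 | 180 × 0.50 = 90 |

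The stated 180 is reproduced exactly at 45%. The largest drop-out it covers is 1 − 99/180 = 45%. At 50% the shortfall is 99 − 90 = 9 practices retained, or 198 − 180 = 18 practices recruited.

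**2. Which difference the 99 belongs to.** Design effect = 1 + (86 − 1) × 0.08 = 7.8. With the usual two-proportion formula and no continuity correction, an assumed 60% to 70% (or 30% to 40%) needs 356 patients per arm before clustering. Then 356 × 7.8 / 86 = 32.3, so 33 practices per arm and 99 in total. A 15-point difference needs only 39 to 48 practices in total for assumed baselines of 20-60%. The 99 is therefore consistent with the 10-point difference, and that is the one exposed to attrition.

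**3. Power for the 10-point difference with 90 practices.**

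- *If 99 practices give exactly 80%:* power = Φ[(1.960 + 0.842) × √(90/99) − 1.960] = Φ(0.711) = 76.2%. This needs no baseline proportion.
- *With the assumed 60% to 70%:* the effective sample per arm is 33 × 86 / 7.8 = 364 at 99 practices and 30 × 86 / 7.8 = 331 at 90. Power goes from 80.9% to 77.0%.

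**4. Power at the lower end of the range.** At 40% drop-out 108 practices remain. The same two calculations give 83.3% and 84.1%.

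**5. Power for the 15-point difference with 30 practices per arm.** For assumed baselines of 20, 30, 40, 50 and 60%, power is 99.2, 98.0, 97.3, 97.5 and 98.6%.

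**The case against.** The strongest reply is that nothing has been miscalculated. The figure of 180 follows exactly from 99 and 45%, and planning on the midpoint of an uncertain estimate is a legitimate choice. The text gives 180 as a minimum and never claims that it covers the worst case. This stands: the fault is that the rate used is not written down, so the printed range and the printed target do not match at the upper end.

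A reader might go further and infer that the 80% power fails throughout the drop-out range, or that the trial is underpowered generally. The document does not support that. From 40% to 45% drop-out at least 99 practices remain, and the 15-point difference is hardly affected even at 50%. Nor does the check show any error in the 99. That figure is reproduced under plausible baselines, and a journal article may leave the baseline to the full protocol or the cited source.

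It is also fair to say that the power figures depend on unstated inputs. The article used a named calculator that handles clustering of both GPs and patients, and its exact formula is not visible. The figures should therefore be quoted only with their assumptions. That 90 is fewer than 99 needs none of them.

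The article also describes Network funding weighted towards recruiting and retaining practices (Incentives for GPs, practices and Networks). This may reduce attrition, but it is not a numerical margin and does not close the gap.

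**Conclusion.** The point holds in a limited form. The target of 180 keeps the plan's own requirement for drop-out up to 45%, not up to the 50% that the same sentence allows. At 50%, 9 of the required 99 practices are missing, and power for the 10-point ACE-inhibitor difference is about 3 to 4 percentage points lower than with 99 practices.

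The count of practices rests on the document's figures alone. The power loss rests on the assumptions listed in the working. If 99 is the true requirement (33 per arm, rounded up from more than 32), 30 per arm falls below 80% whatever the baseline. The issue is minor and does not call the design into question.

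**What to change.** Replace the drop-out sentence in Sample Size estimations with wording to this effect:

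> 180 practices allow for drop-out of up to 45%. At 50% drop-out 90 practices remain (30 per arm with equal allocation), and power for the 10-point ACE-inhibitor difference falls slightly below 80%, to about 76-77%. This assumes a two-sided 5% test, a pairwise comparison of arms, and that 99 practices give 80-81% power. The 15-point beta-blocker difference remains well powered.

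If the authors prefer not to quote a power figure, the minimum change is to say that 180 corresponds to 45% drop-out and that 198 would be needed at 50%.

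The cost is one sentence and a slightly less favourable power statement at the top of the range. Recruitment began in October 2009, and the baseline and six-month data are already being analysed. No additional practices are proposed and no design decision changes.

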### Eligibility criteria for Networks, practices and GPs

To be eligible to participate, a Network had to agree to promote the study to their practices and GPs, be able to recruit a minimum of 7 and a maximum of 15 general practices, and have the capacity to appoint appropriate personnel (project facilitators and other relevant staff) to support the quality improvement intervention. For practices to be eligible, the practice principal GP had to consent to allow the installation of the data software extraction tool and consent for the data to be securely transferred for analysis. Consent was obtained from GPs participating in the PDGPD activities.

